### **3.4 Follow-up Plan**

On the day before the parturient's surgery (T0), researchers will collect baseline data, and assess sleep at T0 on the morning of the surgery. On the day of the surgery, before the first intervention (T1), blinded researchers will evaluate the peak uterine contraction pain and incision pain. After the first intervention (T2), depression and anxiety will be assessed, followed by re-evaluation of peak uterine contraction pain and incision pain during this period. Sleep at T2 will be assessed on the morning of the first postoperative day. Before the second intervention (T3), peak uterine contraction pain and incision pain will be evaluated. After the second intervention (T4), depression, anxiety, postpartum recovery quality, and peak uterine contraction pain and incision pain during this period will be assessed. Sleep at T4 will be evaluated on the morning of the second postoperative day. Before the third intervention

(T5), peak uterine contraction pain and incision pain will be evaluated. After the third intervention (T6), depression, anxiety, postpartum recovery quality, and peak uterine contraction pain and incision pain during this period will be assessed. On the morning of the third postoperative day (T7), sleep at T6 will be evaluated, along with peak uterine contraction pain, incision pain, depression, anxiety, and postpartum recovery quality. At 1 month postpartum (T8), the telephone follow-up will assess the parturient's depressive and anxiety status.

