#### **3.5.2 Secondary outcomes**

1) Peak uterine contraction pain scores during the three days postoperatively (assessed by the VAS). The contraction pain scores are measured before the

first intervention (T1), after the first intervention (T2), before the second intervention (T3), after the second intervention (T4), before the third intervention (T5), after the third intervention (T6), and the third postoperative day (T7).

2) Incision pain scores at T1-T7 (assessed by the VAS).

3) Maternal anxiety scores at T2, T4, T6, T7 and the first month postpartum [T8] (assessed by the Pregnancy-Related Anxiety Questionnaire-Revised 2 [PRAQ-R2], comprising 10 items, each rated on a 5-point scale [1-5], with higher scores indicative of increased pregnancy-related anxiety).

4) Maternal depression scores at T2, T4, T6, T7, and T8 (assessed by the Edinburgh Postnatal Depression Scale [EPDS], including 10 items, scored on a 4-point scale [0-3], with higher scores denote more severe depressive symptoms).

5) Sleep quality at T2, T4 and T6 (assessed by the Leeds Sleep Evaluation Questionnaire [LSEQ], with higher scores indicating better sleep quality).

6) Quality of postpartum recovery at T4, T6 and T7 (assessed by the 11-item Obstetric Quality Recovery Scale [ObsQoR-11], with a total score range of 0-110).

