### **3.6 Statistical Analysis**

Descriptive statistics will include the Chi-squared test or Fisher exact test for categorical variables expressed as frequency. Assessment for normal distribution will be performed with the Shapiro–Wilk test. Normally distributed data will be presented as mean and standard deviation (SD) and compared by the independent sample t-test. Non-normally distributed data will be presented as median and interquartile range (IQR) and compared by the Mann-Whitney U test.

For data collected at multiple time points, we will adopt the Generalized Estimating Equations (GEE). First, we will test the interaction between treatment and time. If this interaction is significant, we will test the between-group differences at each time point and use the Bonferroni test to adjust for multiple comparisons. Otherwise, we will next test the main effect of treatment, and the Bonferroni correction will not be performed for the treatment effects at each time point. For the comparison of the incidence rate of moderate to severe postpartum contraction pain, the GEE model will include the following settings: covariates: intervention group, time, intervention  $\times$  time interaction; link function: logit function; group variable: participant; intraclass

correlation structure: independent. The GEE models for contraction pain score, incision pain score, depression score, anxiety score, sleep score, and recovery quality score will include the following settings: covariates: intervention group, time, intervention  $\times$  time interaction; link function: identity link; group variable: participant; intraclass correlation structure: independent. Data will be analyzed using SPSS version 27.0 (IBM Corp., Chicago, ILUSA) and GraphPad Prism V.9 (GraphPad Software, San Diego, CAUSA), with  $P < .05$  considered statistically significant.

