### **3.7 Sample Size Calculation**

Based on our preliminary observation, the incidence of moderate to severe uterine contraction pain on the third postoperative day following a lower-segment transverse cesarean delivery is approximately 35% (7 out of 20 patients). Considering that the number needed to treat for a moderate treatment effect for neuropathic pain is 4-10, we set the NNT at 5 and the absolute risk reduction (ARR) between the control and the intervention groups as 0.2. Given the ARR value of 0.2, we hypothesized that after three sessions of the active taVNS, the incidence of moderate to severe uterine contraction pain on the third postoperative day would be reduced to 15%. The sample size calculation for comparing two proportions was performed using the Z-Test with Unpooled Variance. The power calculation employed the Normal Approximation method, with a Two-Sided Alternative Hypothesis specified to assess statistical significance of the proportional difference. The

test type was defined as Unpooled Z-Test to accommodate potential between-group variance heterogeneity. A strategy of equal sample allocation ( $N_1 = N_2$ ) was adopted, with input parameters specified as proportions. With a statistical power of 0.80 and  $\alpha = 0.05$ , we calculated that a sample size of 70 patients per group was required using PASS version 15.0 (NCSS). Assuming a 10% loss to follow-up, we planned to recruit 78 participants per group.

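### Pre-treatment pain (T1) is planned as an outcome visit and no model adjusts for a baseline value, which weakens the pain-score analyses and forgoes precision at the primary time point

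*Protocol*

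**What the plan says.** Section 3.4 sets the T1 assessment on the day of surgery: "before the first intervention (T1), blinded researchers will evaluate the peak uterine contraction pain and incision pain". It also has the researchers "assess sleep at T0 on the morning of the surgery".

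Section 3.5.2 then treats T1 as an outcome time. Contraction pain is listed at seven times, T1 to T7, and the next item reads "Incision pain scores at T1-T7 (assessed by the VAS". Sleep is an outcome at T2, T4 and T6 only; T0 does not appear.

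Section 3.6 applies GEE to all data collected at several time points. For the incidence of moderate to severe contraction pain it says "the GEE model will include the following settings: covariates: intervention group, time, intervention" by time. The models for contraction pain, incision pain, depression, anxiety, sleep and recovery have the same three terms. All use an independent working correlation. The group-by-time interaction is tested first. If it is significant, groups are compared at each time point with Bonferroni adjustment; otherwise the main effect of treatment is tested.

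**The concern.** Stimulation cannot affect a score taken before it starts. Such a score is most useful on the right-hand side of the model, where it explains variation between women. As an outcome visit it explains nothing about later visits: with a full group-by-time model and independent working correlation, each visit's contrast is just that visit's raw group difference. T1 also enters the group comparison with a true effect of zero.

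Three things are at stake: the size of the averaged effect for the pain scores, the meaning of the interaction test that chooses between the two analysis branches, and precision for outcomes whose baseline value is already collected. Section 3.6 names the covariates itself, so this is a choice the protocol has made and not a detail left open for the SAP.

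**Working it through.** **Inputs from the protocol (Section 3.7).** Control incidence "approximately 35% (7 out of 20 patients"), so 0.35; active arm: "the incidence of moderate to severe uterine contraction pain on the third postoperative day would be reduced to 15"%, so 0.15; "with a Two-Sided Alternative Hypothesis specified"; power 0.80, alpha 0.05; calculation "performed using the Z-Test with Unpooled Variance"; 70 per group, 78 with 10% loss.

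**Assumed.** Correlations between T1 and later scores, and an equal correlation rho between all seven pain visits. The protocol gives neither.

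**1. The plan's own figure.** The variance sum is 0.35×0.65 + 0.15×0.85 = 0.355. Then n = (1.960 + 0.842)² × 0.355 / 0.20² = 69.66, so 70, and 70/0.9 = 77.8, so 78. Both reproduce. Unadjusted power at 70 per group is Φ(0.20/√(0.355/70) − 1.96) = 80.2%.

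**2. Main-effect branch, pain scores.** With effect δ at T2-T7 and zero at T1, the seven-visit average is 6δ/7 = 0.857δ, whatever the correlation. Example: δ = 0.40 SD, 70 per group, rho = 0.5. The variance of a woman's mean is (1+6rho)/7 = 0.571 over seven visits, (1+5rho)/6 = 0.583 over six, and 0.583 − rho² = 0.333 over six after adjustment for T1. The standard error is √(2 × variance/70).

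| Analysis | Effect (SD) | SE | Power |
|---|---|---|---|
| T1-T7 as outcomes | 0.343 | 0.128 | 77% |
| T2-T7, unadjusted | 0.400 | 0.129 | 87% |
| T2-T7, adjusted for T1 | 0.400 | 0.098 | 98% |

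A simulation of 4,000 trials agreed (estimates 0.342, 0.400 and 0.400). These powers do not condition on the interaction test having been non-significant.

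**3. The interaction test.** Zero at T1 and δ at six later visits is itself a group-by-time interaction. The squared deviations of the visit effects sum to δ² × 6/7 = 0.16 × 0.857 = 0.137. The noncentrality of the 6-df test is 0.137 × 70 / [2(1 − rho)], which is 9.6 at rho = 0.5. The test then rejects in 36%, 46%, 62% and 87% of trials at rho = 0.1, 0.3, 0.5 and 0.7, although the effect does not vary after treatment starts. Those trials go to per-visit comparisons at 0.05/7 = 0.00714. Without T1 the threshold would be 0.05/6 = 0.00833.

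**4. Primary time point, T7.** In a fitted independence GEE with full group-by-time terms, the T7 coefficient equalled the raw difference (identity link) and the raw log odds ratio (logit link). T1 in the model therefore neither shifts nor sharpens it.

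To size the gain from adjusting for continuous T1 VAS, take T1 and T7 as latent bivariate normal with correlation r. Given T1 = x, the T7 risk is m(x) = Φ[(Φ⁻¹(p) + r·x)/√(1 − r²)]. The adjusted variance V is E[m(1 − m)] summed over the two arms, plus half the variance of the difference between the arms' m(x). Power is Φ(0.20/√(V/70) − 1.96).

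| r (assumed) | V | Variance cut | Power |
|---|---|---|---|
| unadjusted | 0.355 | 0 | 80.2% |
| 0.1 | 0.353 | 0.5% | 80.4% |
| 0.3 | 0.338 | 4.7% | 82.0% |
| 0.6 | 0.284 | 20.0% | 88.1% |

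The last two rows correspond to about 73 and 87 women per group without adjustment (70 × 0.355/V).

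**5. Sleep.** T0 is not among the outcome visits, so nothing is diluted. For a continuous score, adjustment cuts the variance of a single-visit contrast by r²: 25% at r = 0.5 and 49% at r = 0.7, if correlations are that high.

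**The case against.** The best defence is that the primary comparison is sound as planned. It is a single-time-point contrast, the model leaves it equal to the raw comparison, type I error is not inflated, and the sample size was computed for exactly that unadjusted comparison. All of this stands. A reader might infer from the T1-T7 listing that the primary effect is diluted; it is not. Section 3.6 does not even list the visits for the incidence model, so T1's presence there is an inference.

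The gate also limits the 6/7 figure. A constant effect with zero at T1 often triggers the interaction, so many trials never reach the diluted average. This stands too, but those trials move to the Bonferroni branch because of a visit that treatment could not affect.

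The gain may be small. T1 is taken on the day of surgery after spinal-epidural anaesthesia, about three days before T7, so a weak correlation is plausible; at r = 0.1 the gain in power is 0.2 points. It would be tempting to call T1 pain and T0 sleep the strongest available predictors, but the protocol has no data to show it. Nor does it say whether the allocation envelope is opened before or after the T1 assessment. Only the order of T1 and stimulation is secure, and that is enough for this point.

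Finally, one might blame the independent working correlation. With complete data and a full group-by-time model, an exchangeable structure gives the same contrasts, so that is a matter of preference.

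**Conclusion.** The point holds for the pain-score models and, as lost precision, for sleep and the primary comparison. The protocol fixes a pre-treatment measurement as an outcome and excludes every baseline value from adjustment. In the main-effect branch, a constant T2-T7 effect is reported at 86% of its size; that figure rests on the effect being constant but on no correlation. In the other branch, one of seven Bonferroni comparisons goes to a visit with no possible effect. For the primary contrast the loss is power only, between negligible (r = 0.1) and about 8 points (r = 0.6), on assumed correlations. The textual facts are certain; the size of the precision gain is not. This is an improvement the sponsor should make. It does not make the planned T7 comparison invalid.

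**What to change.** In Sections 3.5.2 and 3.6, and in the SAP, before unblinding:

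- Make T2-T7 the outcome visits for both pain scores, and report T1 as a baseline value. Add T1 contraction-pain VAS as covariate for contraction pain and T1 incision VAS for incision pain. The interaction test then asks only whether the effect varies after treatment has started.
- Add T0 LSEQ as covariate in the model for sleep at T2, T4 and T6.
- Adjust the T7 primary comparison for continuous T1 contraction-pain VAS, and report a standardised (marginal) risk difference, which keeps the effect measure used for sizing.
- List the visits that enter the incidence model.

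All these values are already collected, so the cost is wording. There are two small downsides: the odds ratio from the adjusted logit model becomes conditional, which is why the standardised risk difference is needed, and a woman with a missing T1 or T0 value needs a simple baseline imputation rule. The working correlation need not change.

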### **3.7 Sample Size Calculation**

Based on our preliminary observation, the incidence of moderate to severe uterine contraction pain on the third postoperative day following a lower-segment transverse cesarean delivery is approximately 35% (7 out of 20 patients). Considering that the number needed to treat for a moderate treatment effect for neuropathic pain is 4-10, we set the NNT at 5 and the absolute risk reduction (ARR) between the control and the intervention groups as 0.2. Given the ARR value of 0.2, we hypothesized that after three sessions of the active taVNS, the incidence of moderate to severe uterine contraction pain on the third postoperative day would be reduced to 15%. The sample size calculation for comparing two proportions was performed using the Z-Test with Unpooled Variance. The power calculation employed the Normal Approximation method, with a Two-Sided Alternative Hypothesis specified to assess statistical significance of the proportional difference. The

test type was defined as Unpooled Z-Test to accommodate potential between-group variance heterogeneity. A strategy of equal sample allocation ( $N_1 = N_2$ ) was adopted, with input parameters specified as proportions. With a statistical power of 0.80 and  $\alpha = 0.05$ , we calculated that a sample size of 70 patients per group was required using PASS version 15.0 (NCSS). Assuming a 10% loss to follow-up, we planned to recruit 78 participants per group.

### **3.8 Intervention with taVNS**

On the day of delivery, the first postpartum day, and the second postpartum day, the intervention group received three sessions of active taVNS in total, and the control group received three sessions of sham taVNS in total. Electrical stimulation is applied through electrodes placed on the left concha of the ear (tVNS501; Changzhou Ruishen'an Medical Devices Co., Ltd.). In the active taVNS group, participants receive taVNS (pulse width: 200  $\mu$ s; frequency: 20 Hz) for 30 minutes, with the current increasing for 30 seconds until the participant reports a tingling sensation, then decreasing to a level slightly below this threshold for 30 minutes. In the sham taVNS group, electrodes are positioned similarly, with the current increasing for 30 seconds until the participant reported a tingling sensation, then decreasing to a level slightly below this threshold, after which the device remained off for the following 30 minutes to simulate the sham state. Throughout the intervention, researchers closely monitor participants for any adverse effects and stop the

stimulation immediately if intolerable side effects are observed.

### **3.9 Anesthesia protocol**

Upon entering the operating room, a peripheral intravenous line is established, and standard monitoring of blood pressure, electrocardiogram, and pulse oximetry is initiated. Following skin disinfection, anesthesiologists perform combined spinal-epidural anesthesia after administering a local infiltration of 2% lidocaine. The lumbar puncture is conducted at the Lumbar spine 2 (L2) - L3 or L3 - L4 intervertebral spaces. For the intrathecal administration, 1.0-1.5 ml of 0.75% bupivacaine hydrochloride is intrathecally injected. Subsequently, the spinal needle is removed, and the epidural catheter is advanced 3-5 cm in the cephalad direction within the epidural space. If necessary, an additional 5 ml of 2% lidocaine is administered via the epidural catheter to provide supplemental analgesia. The maximum level of anesthesia is maintained at thoracic spine 4 - thoracic spine 6. Throughout the procedure, oxygen is delivered via a nasal cannula at a flow rate of 2 L/min. Following the delivery of the fetus, intravenous administrations of 0.075 mg palonosetron and 10 mg nalbuphine hydrochloride are performed. Vasopressor agents are administered as required to ensure hemodynamic stability during anesthesia. Postoperative analgesia is administered via a patient-controlled intravenous analgesia pump. The pump is loaded with sufentanil 1.5 µg/kg, nalbuphine 30 mg, and palonosetron 0.15 mg, which are diluted to 120 ml with normal saline. The Patient-Controlled Intravenous Analgesia pump have a loading dose of 2

ml, a basal infusion rate of 2 ml/h, and a self-controlled analgesic dose of 0.5 ml.

#### **4. Data and Safety Monitoring**

The clinical study will implement a comprehensive safety monitoring plan based on a thorough risk assessment. Throughout the study, all adverse events (AEs) will be meticulously documented, promptly addressed, and continuously monitored until resolution or stabilization of the patient's condition. Serious adverse events (SAEs) and unexpected incidents will be reported immediately to the ethics committee, regulatory authorities, and drug oversight agencies as required by the protocol. The principal investigator will conduct periodic comprehensive reviews of all AEs and, if necessary, convene an investigator's meeting to evaluate the risks and benefits associated with the study. This trial is designed as a double-blind study, and blinding will be broken only when necessary to ensure participant safety and rights. Independent data monitoring personnel will be assigned to continuously oversee the study data. For high-risk studies, an independent Data Safety Monitoring Board (DSMB) will be established to review accumulated safety and efficacy data and determine whether the study should proceed.

#### **5. Funding**

This study is supported in part by grants from the National Key R&D Program

of China (2022ZD0206200 to SZ); the Key Technologies R&D Program of Guangdong Province (2023B0303020003 to J-LC); Jiangsu Basic Research Programs (BK20243035 to J-LC); National Natural Science Foundation of China (81720108013, 82293641, 82130033 to J-LC; 82171227 and 81300957 to HL; 81771453 and 31970937 to HXZ; 82371536 to SZ); Zhejiang Provincial Natural Science Foundation (LY22H090019 to HL); open project fund of the Key Laboratory for NeuroInformation of Ministry of Education (202311KFY00102 to HL); the Natural Science Foundation of Shanghai (21ZR1411300 to YH); and Shenkang Clinical Study Foundation of Shanghai (SHDC2020CR4061 to YH).

## **6. Information confidentiality**

Medical records are securely kept at the hospital, and access will be granted solely to authorized investigators and members of the ethics committees. Any public dissemination of the study results will ensure that patient identities remain confidential and anonymous.

